# Diminishing accelerated long-term forgetting in mild cognitive impairment: Study protocol for a prospective, double-blind, placebo-controlled, randomized controlled trial

**DOI:** 10.1016/j.conctc.2022.100989

**Published:** 2022-09-02

**Keywords:** Episodic memory, Amnestic mild cognitive impairment, Mild Alzheimer's disease, Electrical stimulation, Greater occipital nerve

## Abstract

**Background:**

Harnessing the lifelong potential of the human brain for neuroplasticity may serve to maintain the viability of neural structures and postpone the onset of cognitive decline. The absence of effective pharmacological interventions to counter memory decline has encouraged scientists to test the possibility that noninvasive electrical stimulation may serve as an additional tool to improve memory abilities.

Previous research showed that electrical stimulation of the greater occipital nerve enhances memory recall performance in young and older healthy subjects. This study aims to extend these findings to determine the effect of transcutaneous electrical stimulation of the greater occipital nerve on the improvement of episodic memory in individuals with amnestic Mild Cognitive Impairment (aMCI).

**Methods/design:**

This study is a prospective, double-blind, placebo-controlled, randomized parallel-group study. A total of 100 individuals with a diagnosis of aMCI according to NIA/AA will be recruited. Participants will be randomly assigned to one of four groups. One group will receive active non-invasive transcutaneous electrical stimulation of greater occipital nerve (NITESGON), while three groups will serve as controls (i.e., sham NITESGON, active NITESGON with local anesthesia, and active NITESGON on the C5/C6 nerve). The primary outcome, i.e., memory recall, will be determined by a word association task, and will be recorded at baseline, 7 days after NITESGON, and 28 days after NITESGON. The secondary outcome is neurophysiological changes determined by resting state EEG and will be assessed immediately before and after NITESGON.

**Discussion:**

The results will add new insights into improving episodic memory in individuals with aMCI.

**Trial registration:**

#NCT05289804 (clinicaltrial.gov)

**Protocol approval id:**

#SPREC102021-23 (Ethics Committee at Trinity College Dublin, School of Psychology)

## Background

1

Advances in medicine and public health, rising standards of living, and improvements in education and nutrition have lengthened the human life span [1], thereby increasing the prevalence of Alzheimer's disease (AD). The prevalence of amnesic mild cognitive impairment (aMCI), a prodromal stage of AD, is 10–20% in adults aged 65 years or above and increases with age [2]. Researchers posit that early identification and intervention may be the key to mitigate dementia and memory impairments. Deficits in episodic memory, including accelerated long-term forgetting (ALF), are one of the earliest detectable cognitive abnormalities in aMCI and AD [3].

ALF refers to abnormal forgetting over hours to weeks despite normal acquisition or encoding [4]. ALF is believed to be mediated by a disruption in memory consolidation, the memory processing stage in which information is transferred from short-term into long-term memory. The locus coeruleus (LC) plays a key role in driving hippocampal synaptic plasticity required for memory consolidation, in which synaptic connections are modified and strengthened to support the rapid formation of memory events [5,6]. A number of studies have documented abnormal LC activity associated with aMCI and AD [[7], [8], [9], [10], [11], [12], [13], [14]], which likely affects the hippocampal synaptic plasticity necessary for memory consolidation. Interventions that target synaptic plasticity could be promising in managing ALF by improving memory consolidation, and consequently ALF in aMCI subjects.

In a recent study we demonstrated that non-invasive transcutaneous electrical stimulation of greater occipital nerve (NITESGON) improves memory in healthy young (18–25 years) [15] and older (>65 years) [16] participants up to 28 days after stimulation. In the latter study, NITESGON was utilized in an older population to determine if stimulation during an associative memory task can optimize associative memory performance up to 28 days later. Thirty subjects between the ages of 55 and 70 years were enrolled and randomly assigned to active or sham NITESGON group. Active or sham NITESGON was delivered during the study phase at visit 1 of the associative memory task, and participants were asked to return 7-and 28-days later to measure memory recall. During visit 1, participants learned a list of 50 Swahili-English word pairs (e.g., mashua-boat) across a total of 3 blocks for each study (S) and test (T) phase. The study phase of each block consisted of 50-word pairs followed by a test phase of the 50 words, in which participants were asked to type the correct English translation for each Swahili word. Participants were then dismissed and returned for the test 7-days and 28-days later (recall phase). During this test, subjects were shown each Swahili word and were asked to type the correct English translation. This was identical to the test phase from the first visit. Participants that received active stimulation exhibited increased words recalled on days 7 and 28 compared to participants that received sham stimulation (Day 7: η^**2**^ = .21; Day28: η^**2**^ = .14). These findings suggest that NITESGON enhances memory performance up to 28-days after a single session. With these results, we propose that NITESGON could mitigate memory loss and rate of decline in the earliest stages of Alzheimer's disease.

Results also demonstrated that NITESGON promotes noradrenaline (NA) release though LC activation, followed by enhanced communication between the LC and hippocampus. NITESGON induced synaptic plasticity then modulates memory with lasting effects by strengthening memory consolidation after encoding, resulting in upregulated memory performance [15]. Furthermore, we were able to show that NITESGON induces gamma changes in the medial temporal lobe immediately after NITESGON, which was correlated with successful recall several days after stimulation. This latter finding suggest that gamma oscillations can potential be use as a biomarker for successful recall.

We seek to extend these findings to determine if NITESGON can enhance memory consolidation in aMCI subjects. To do so, we will use the word association task to assess whether NITESGON can mitigate ALF in individuals diagnosed with aMCI. In addition, we plan to assess the effect of NITESGON on EEG activity by examining the association of gamma oscillations in the medial temporal cortex with memory performance. We hypothesize that NITESGON can improve memory performance to mitigate ALF in aMCI subjects by targeting and strengthening the impaired hippocampal neuroplasticity necessary for memory consolidation. Demonstrating NITESGON induced memory improvements will be a significant step forward towards developing an effective treatment and potential early intervention for individuals with aMCI.

## Method/design

2

### Aims

2.1

The objective of current project is to establish the effectiveness of NITESGON in decreasing ALF in individuals with aMCI. Our primary hypothesis is that participants that receive active NITESGON while learning a word association task will perform better on word recall 7 and 28 days after NITESGON in comparison to control groups. In addition, we hypothesize that active NITESGON will significantly increase gamma oscillations within the medial temporal cortex after NITESGON in association with memory performance in individuals with aMCI 7 and 28 days after NITESGON.

### Ethics

2.2

This study is approved by the Trinity College Data Protection Office and is in compliance with data protection legislation, specifically the EU General Data Protection Regulation 2016 (‘GDPR’), Data Protection Acts 1988–2018 and Health Research Regulations 2018. It was further approved by the Ethics Committee at Trinity College Dublin, School of Psychology (**#**SPREC102021-23).

### Study design

2.3

This study is designed as a prospective, double-blind, placebo-controlled, randomized parallel-group study that will be completed at Trinity College Dublin, Ireland. A total of 100 individuals with amnestic mild cognitive impairment (aMCI) based on diagnostic criteria described by the National Institute on Aging and Alzheimer's Association [17] will be recruited from Alzheimer's Ireland. Subject will receive a (real or control) non-invasive transcutaneous electrical stimulation of the greater occipital nerve (NITESGON) procedure. After providing written informed consent, subjects will be assigned to one of four groups. One group will receive active NITESGON, while the three groups will be control groups. One group will receive sham NITESGON (inactive control), while a second group will receive active NITESGON with local anesthesia (active control; local nerve anesthesia group) and a third group will stimulate the C5/C6 nerve (active control; same sensation different nerve). We will include three control groups so that we are able to verify that the effect is real, location specific and cannot be associated to a sensation effect.

We have opted to use a parallel-group design as it is unclear what the carry-over effect and/or wash-out period will be for NITESGON. Subjects will be randomized after screening evaluation and will be assigned to receive one of the four possible types of NITESGON. To eliminate subjective bias, all subjects and the investigator testing the endpoint measures will be blinded to the type of intervention. The researcher who will control the NITESGON device will not be involved in instructing the participant; this will be performed by a second researcher who will be blind to the stimulation protocol. The primary outcome will be change in memory performance as measured by a word association task, measured at baseline (T0), 7 days after NITESGON (T1) and after 28 (T2) days after NITESGON. Secondary outcomes include changes in resting EEG, which will be assessed immediately before and after NITESGON (see Fig. 1 and Table 1).

**Fig. 1 fig1:**
[figure not shown]
Participant flow through study.

**Table 1 tbl1:** Data collection timepoints.

	T0	T1	T2
	Baseline	7 days after NITESGON	28 days after NITESGON
Word association task	x	x	x
Neurophysiology	x		
Adverse events	x		
Blinding			x
Control assessments	x		

### Recruitment and screening

2.4

We plan to include 100 English-speaking individuals with aMCI, recruited from Alzheimer's Ireland. Individuals will be referred to the study once a general practitioner has confirmed the diagnosis according to the Albert et al. [17] criteria. Individuals will be referred to the study nurse who will explain the study in detail and go through the eligibility criteria to see if the patient is interested in participating. If interested and eligible, the study nurse can schedule an appointment for a first visit. Additionally, patients who sought care at the memory clinic at St. James or Tallaght University Hospital for aMCI in the past will be contacted for this study if they had indicated they were interested to participate in future research studies. Advertisements will also be simultaneously implemented to recruit outside the network.

Participants will be screened and included in the study irrespective of their race. We will exclude non-English speakers because not all screening forms, questionnaires and tests are available or validated in any other language except English. To participate in this study, subjects should be able to provide an informed consent, have a confirmed aMCI diagnosis from their general practitioner and have all medications stable for at least three months prior to baseline data collection.

*Diagnostic criteria.* Participants will have a diagnosis of aMCI according to the Albert et al. [17] criteria. All enrolled participants will be classified as having memory decline based on the Clinical Dementia Rating global score of 0.5 or greater, consistent with the established classification [17,18].

*Inclusion Criteria*. One-hundred individuals, 50 years of age and above with amnestic mild cognitive impairment (aMCI) will be recruited. Participants who meet the following criteria will be eligible to participate: (1) Diagnosis of probable aMCI; (2) Montreal Cognitive Assessment between 18 and 25; (3) stable medication condition for more than 3 months; (4) stable medical condition for more than 6 months; (5) adequate visual and auditory acuity to complete neuropsychological testing; (6) capacity to provide written and dated informed consent form. Prospective participants, who meet the criteria, will be sent an electronic copy of the consent form. Participants will only be asked to sign the consent form at the site after going over the form with the researcher where all aspects of the study protocol will be reviewed.

*Exclusion criteria*. Participants will be deemed ineligible if they meet any of the following criteria: (1) any cause of cognitive decline or dementia that is not Alzheimer's disease related; (2) enrollment in any investigational drug study; (3) history in the past 2 years of epileptic seizures (participants with epilepsy who have been stable off medication or seizure free for 2 years may be included); (4) any major psychiatric disorder (a clinical diagnosis of major depressive disorder, bipolar disorder, or schizophrenia); (5) past history or MRI evidence of brain damage, including significant trauma, stroke, hydrocephalus, intellectual disability, or serious neurological disorder; (6) significant history of alcoholism or drug abuse of non-prescription drugs within the last 10 years; (7) familiarity with Swahili/Arabic language or Swahili culture due to the nature of the stimuli; (8) MCI due to vascular disease. Participants will be invited to complete MRI brain scans. Participants with pacemakers or other medical metal devices that are incompatible with MRI will not be eligible for MRI scanning as per standard procedures.

*Withdrawal of participants.* The investigator can decide to withdraw a subject from the study for urgent medical reasons. Subjects can leave the study at any time for any reason if they wish to do so without any consequences.

### Study procedure

2.5

We will conduct this study as follows:(1)Screening of individuals with aMCI.(2)Randomly assigning aMCI subjects to one of the four NITESGON groups.(3)Administering one session of 1.5-mA active (*n* = 25) or control (*n* = 25 in each of three control group) NITESGON paired with a word-association task; administered by research assistant.(4)Behavioral assessments after each of the three blocks of studying the word associations and neural measures immediately after the last session of Behavioral assessments (T0).(5)Behavioral assessments at seven (T1) and 28 (T2) days after NITESGON.

### Intervention

2.6

NITESGON will be delivered by a specially developed, battery-driven, constant current stimulator with a maximum output of 10 mA (http://www.neuroconn.de) via a pair of saline-soaked surface sponges (35 cm^2^) on the scalp. One electrode will be placed over the left and right C2 dermatomes each. A constant current of 1.5 mA intensity will be applied during each of the 3-study phases (i.e., 250 s x 3 blocks). For sham NITESGON, placement of the electrodes will be identical to active NITESGON. A third group (local nerve anesthesia group) will receive NITESGON, but we will use a topical skin anesthetic (lidocaine/prilocaine cream) to reduce any potential contribution from transcutaneous stimulation of peripheral nerves. This lidocaine/prilocaine preparation blocks sodium channels in peripheral nerves in the skin and thereby stabilizes the membrane potential and increases the threshold for firing an action potential [15,19]. For the fourth control group (different nerve group), the electrodes will be placed over cervical nerves five and six, to mimic the sensation, but change the location. For both the third and fourth control group, we will apply the same current as active NITESGON. NITESGON will first be switched on in a ramp-up fashion over 30 s. For sham, the current intensity (ramp down) will gradually be reduced (over 5 s) as soon as NITESGON reaches a current flow of 1.5 mA. The rationale behind this sham procedure is to mimic the transient skin sensation at the beginning of active NITESGON without producing any conditioning effects on the brain.

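### The masking described supports the double blind only for active against sham; it is not secured for the anaesthesia and C5/C6 comparisons, and the blinding test omits both arms

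*Protocol article*

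**What the plan says.** The design statement in section 2.3 (Study design) reads: "This study is designed as a prospective, double-blind, placebo-controlled, randomized parallel-group study". It adds that "all subjects and the investigator testing the endpoint measures will be blinded to the type of intervention". The mechanism given is a division of labour. One researcher runs the device and does not instruct the participant; of the instructing, the article says "this will be performed by a second researcher who will be blind to the stimulation protocol".

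Section 2.6 (Intervention) sets out how the arms look:

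- Sham: "For sham NITESGON, placement of the electrodes will be identical to active NITESGON". The current is ramped up as in active and then ramped down.
- Anaesthesia control: "A third group (local nerve anesthesia group) will receive NITESGON, but we will use a topical skin anesthetic (lidocaine/prilocaine cream". No cream of any kind is mentioned for the other arms.
- Different-nerve control: "the electrodes will be placed over cervical nerves five and six, to mimic the sensation, but change the location".

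Section 2.7.2 asks participants at T2 whether they believe they were in the control or the active group, with no restriction by arm. Section 2.10 then tests guess against allocation by chi-square for active and sham only.

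**The concern.** Separating the operator from the instructor hides whether current is flowing. That is what has to be hidden between active and sham, where the set-up is otherwise the same. The other two controls receive the same current as active and differ from it in what is put on the skin or where the electrodes sit. Keeping the instructor away from the device controls hides neither.

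Section 2.3 gives the three controls distinct purposes: to show that an effect is real, that it depends on the site stimulated, and that it is not produced by sensation. The last two rest on the arms whose masking is not described. Stimulation is given while the word pairs are being learned. An instructor who recognises the arm, or a participant who guesses it, could therefore alter engagement, effort or expectation as the memory is formed. A better result in the active arm might then be read as nerve specificity when part of it is expectancy. With the blinding test confined to active and sham, the planned analysis would not reveal this.

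**Working it through.** The plan gives no figure on this point to reproduce. The check sets the sections side by side, then counts.

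**1. Set-up of each control against active** (sections 2.3 and 2.6)

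| Control arm | Difference from active | Hidden by the described masking? |
|---|---|---|
| Sham | Current only; same placement, same ramp-up | Yes: operator separation and ramp |
| Anaesthesia | Cream described for this arm alone | Nothing described |
| C5/C6 | Electrode site | Nothing described |

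**2. Who could notice, and when.** Section 2.5 places "Behavioral assessments after each of the three blocks of studying the word associations" in the stimulation session, so learning, stimulation and T0 testing are interleaved. An instructor present at that session could see the site or the cream. For participants, section 2.4 says the consent form is signed "after going over the form with the researcher where all aspects of the study protocol will be reviewed". Someone who has been told of an arm with numbing cream, and is then given it, may infer the allocation.

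**3. Count** (25 per arm, section 2.5)

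- Participants in the two arms: 2 × 25 = 50 of 100 overall, and 50 of 75 controls.
- Comparisons with active affected: 2 of 3.
- Participants in the planned blinding test: 25 active + 25 sham = 50 of 100, with none from the two arms at issue.

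**4. Illustration of what an expectancy shift would do.** The shifts are assumed and have no source in the article. Take two arms of 25, no true effect, a bias of d standard deviations in favour of active, and a one-sided test, since section 2.10 specifies directional hypotheses. By normal approximation the false-positive probability is P(Z > z − d√(25/2)), with √12.5 = 3.536.

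| d (assumed) | d × 3.536 | One-sided 5% (z = 1.645) | One-sided 2.5% (z = 1.960) |
|---|---|---|---|
| 0.1 | 0.354 | 0.098 | 0.054 |
| 0.2 | 0.707 | 0.174 | 0.105 |
| 0.3 | 1.061 | 0.280 | 0.184 |

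This is a simple two-sample contrast, not the mixed-model interaction contrast that is planned. It shows how an assumed bias would carry through and is no evidence that such a bias exists.

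**The case against.** The strongest reply is that silence is not absence. A journal article condenses its protocol. Use of a dummy cream, covering of the sites and who prepares the skin may all be in the full document. A reader might infer from section 2.6 that the other arms get no cream at all, or that the blind is bound to fail in two arms. The article supports neither reading. It does not say what the other arms receive on the skin, whether the instructor stays in the room or can see the sites, or whether cream would be visible under the sponges.

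Other points also limit the concern:

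- The design is parallel-group, so each participant sees one set-up. C5/C6 stimulation is meant to feel the same as active, and a participant there would need to know which site is the hypothesised one. The consent wording is not shown, so unblinding of C5/C6 participants is not demonstrated. Knowing that a numbing cream was used is likewise not the same as knowing that one is a control.
- Section 2.3 also blinds the endpoint tester. Recall at T1 and T2 is typed and computer-paced, so a tester who was not at the T0 session can remain blind and has little room to influence the result.
- At T0, too, presentation and test times are fixed and failed items receive no feedback. This narrows the route through instruction, though not the one through effort or expectation.
- The sham comparison is untouched.

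All of this stands against a claim that blinding must fail. It does not remove the mismatch within the text. The article does describe its masking, and what it describes fits one comparison while the claim covers four arms. The restriction of the blinding test to active and sham is stated outright and is not a matter of condensed detail.

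**Conclusion.** The concern holds in a limited form. As described, the masking supports the stated double blind for active against sham only. For active against anaesthesia and active against C5/C6 (2 of 3 control comparisons, 50 of 100 participants), blinding of the instructing researcher at T0 is not secured. Nor is that of participants in the cream arm. The planned blinding test would not detect a failure in either arm.

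This rests on two readings: that the differences described in section 2.6 are visible during set-up or learning, and that no concealment is in use beyond what the article describes. If the full protocol already provides a dummy cream and covered sites, what remains is to say so and to widen the blinding analysis.

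The stronger conclusion, that the double blind cannot hold in these arms, does not follow from the document. The size of any bias is unknown, and the 0.1 to 0.3 SD shifts are illustrative assumptions. The point should be acted on because the specificity conclusions depend on these two comparisons and the remedy is cheap.

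**What to change.** 1. **Conceal the set-up at T0.** Have the device operator, who is already unblinded, do all skin and electrode preparation and cover both the C2 and C5/C6 sites before the instructing researcher enters. State that T1 and T2 testers were not present at the T0 set-up. This needs a cover, some preparation time and suitable rostering of the testers; no new role is added.
2. **Widen the blinding analysis.** Use the question already put at T2, and report guess by allocation for all four arms instead of active and sham alone. This adds no data collection.
3. **Match appearance where feasible.** Use an inert cream in the arms without anaesthetic, and unconnected sponges at the unused site in every arm. The cost is materials and extra preparation time at the single stimulation visit. First check that cream under the electrodes does not alter the active procedure; if it might, leave the cream out and rely on steps 1 and 4.
4. **Otherwise, limit the claim.** If appearance is not matched, restrict the double-blind statement in section 2.3 to active against sham, and report the anaesthesia and C5/C6 comparisons as not fully masked. This costs only wording and a narrower claim.
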